## Discussion

This trial is the next logical step to the feasibility study conducted by our research team on 12 post-proximal humerus facture patients [31]. The previous study demonstrated that telerehabilitation seems to be a promising avenue to provide rehabilitation services to this population without adverse events. The results obtained following the present protocol will affirm the cost-efficacy of telereahabilitation treatment in an orthopaedic context, more precisely, after a proximal humerus fracture treated conservatively.

In order to control a potential selection bias, randomisation will be blind to the evaluator and participants’ characteristics will be compared pre-intervention between each group. If a group differs on some characteristics despite randomisation, corrective measures will be made in subsequent analyses. Furthermore, information bias will be controlled by using standardized measures and by calibrating all the assessors for each assessment.

This study will verify the noninferiority of in-home telerehabilitation compared to face-to-face intervention at a clinic for patients with proximal humerus fracture. In accordance with our hypothesis, we think that telerehabilitation will improve access to a rapid, less expensive, satisfactory and effective rehabilitation services.

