**Methods/Design:**

In this randomized controlled trial, individuals who have had a proximal humerus fracture treated conservatively at the Centre intégré universitaire de santé et de services sociaux de l’Estrie - Centre hospitalier universitaire de Sherbrooke (CIUSSS de l’Estrie CHUS), and who are returning home will be included. Participants will be recruited during their visit to the emergency ward or outpatient clinic by the medical or research team and will then sign the informed consent form if they are interested to participate in the study. We expect to recruit 52 participants (26 per group). Randomization will be done by a random number generator with sealed envelopes. Each patient will be evaluated before the beginning of the rehabilitation (T1), and immediately after the 2-month intervention (T2). The following outcomes will be measured: 1) upper extremity function (Constant Shoulder Score and Disability of the Arm, Shoulder and Hand questionnaire [DASH]); 2) range of motion (conventional goniometer); 3) user satisfaction (Health Care Satisfaction questionnaire); and 4) cost of services to the public healthcare system.

The difference between the two groups will be compared using a *t*-test or a chi-squared test, and through a cost-effectiveness economic analysis.

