### Dependent variables

Participants will attend a total of two evaluations of approximately 1.5 h each with a trained research assistant at the Research Centre on Aging before (T1) and after (T2) the intervention period. Each assessment will be executed in the same order to optimise the validity of the collected information: 1) range of motion (flexion, extension, abduction, external and internal rotation); 2) upper limb function; 3) global shoulder function and pain; and 4) participant satisfaction. Every item will be evaluated at both assessments, except for the satisfaction, which will be assessed only at T2.

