#### Shoulder functional measures

Shoulder global function will be measured with the Constant score [36], which is the primary outcome measure. This questionnaire allows the assessment of four outcomes related to shoulder function: 1) pain; 2) activities of daily living (sleeping, work, leisure); 3) range of motion; and 4) muscle strength. The total is on 100 and a higher score indicates a higher shoulder function. According to a systematic review of the psychometric properties of the Constant score, the reliability of this questionnaire is excellent (ICC, 0.89; 95 % confidence interval, 0.79–0.94) [37], and the internal consistency, evaluated with the Cronbach alpha, ranges from 0.60 to 0.75 suggesting that it measures different aspects of function [38, 39].

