### Statistical methods

The principal analyses intend to test the noninferiority of the TELE intervention versus the CLINIC intervention. We aim to recruit a total of 52 participants, or 26 participants per group. Sample size was determined with data from a previous study on the Constant score [44], which is considered in this study as the primary outcome measure. With 26 participants per group, within the context of a unilateral t-test with an alpha level set at 0.05, the power of the study to reject non-equivalence hypothesis would be at 69 % for a difference of 10.3 or less (standard deviation = 17). This noninferiority point is under the minimal clinically important difference of 10.4 points on the Constant score [44].

Participant characteristics in each group will be described pre-intervention (T1) using mean and standard deviation (continuous variables) or proportion (categorical variables). Groups at baseline will then be compared using *t*-test or chi-squared test.

First, the data will be analysed according to the received intervention (per protocol), and then, according to the assigned group (intention to treat analysis). A sensitivity analysis will be used to explore the effect of compliance or screen failures: missing data will be replaced by extreme data (no change following intervention or most favorable change noted in the study). Any non-robustness of the revealed results by comparison of strategies will be noted.

Economic analysis is of cost-efficacy type. Cost by change-unit of the principal dependant variable (Constant score) will be determined for both groups. Differential cost will then be established.

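### Adjustment of the group comparison depends on observed baseline differences, with characteristics, threshold and method unnamed, and the T1 Constant score is not a prespecified covariate

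*Protocol article*

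**What the plan says.** **Outcome and timing.** The section on shoulder functional measures states: "Shoulder global function will be measured with the Constant score [36], which is the primary outcome measure". Under Dependent variables: "Every item will be evaluated at both assessments, except for the satisfaction, which will be assessed only at T2". So every participant assessed at T1 has a baseline value of the primary outcome.

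**Group comparison.** The abstract says "The difference between the two groups will be compared using a" t-test or a chi-squared test. Statistical methods sets the aim, "The principal analyses intend to test the noninferiority of the TELE intervention versus the CLINIC intervention", and bases the sample size on a t-test: "With 26 participants per group, within the context of a unilateral t-test with an alpha level set at 0.05". The stated power is 69% for a difference of 10.3 points with SD 17. No covariate is named. Nothing says whether the t-test is on the T2 score or on the T1–T2 change.

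**Baseline comparison and its consequence.** Statistical methods: "Groups at baseline will then be compared using *t*-test or chi-squared test". The Discussion, in a paragraph on controlling selection bias, adds: "If a group differs on some characteristics despite randomisation, corrective measures will be made in subsequent analyses".

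**The concern.** Under sound randomisation, a baseline difference between arms is a chance difference. A test of it does not show whether the variable is prognostic. With 26 per arm, such tests miss many imbalances that matter and flag some that do not. A rule that adjusts only after such a difference appears makes the final analysis depend on the data.

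Here the rule is also open. It names no candidate characteristics, no criterion for a difference, and no remedy: covariate adjustment, stratification, change scores and a secondary sensitivity analysis would all fit the wording. In a noninferiority trial, where the conclusion rests on one confidence limit against a 10.3-point margin, that leaves room to choose the estimate after seeing the results.

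The second cost is efficiency. The trial accepts 69% power, so about three in ten trials of truly equal treatments would fail to show noninferiority. A baseline score that could reduce the residual variance is already collected but has no fixed place in the analysis.

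**Working it through.** **Inputs from the article (Statistical methods).** n = 26 per arm, margin 10.3, SD 17, one-sided alpha 0.05, stated power 69%.

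**Assumptions, not in the article.** True difference 0; SD 17 is the SD of the T2 score, with equal SD at T1; T1–T2 correlation r between 0.1 and 0.7; number of baseline characteristics tested; significance trigger at two-sided 5%.

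**1. The plan's own figure.** SE = 17 × √(2/26) = 4.715. Noncentrality = 10.3 / 4.715 = 2.185. With 50 df and a one-sided critical value of 1.676, power from the noncentral t is 69.5% (normal approximation 70.5%). The stated 69% is reproduced, and it is the power of an unadjusted comparison.

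**2. T1 as a prespecified covariate.** Residual SD = 17 × √(1 − r²), 49 df.

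| Assumed r | Residual SD | Noncentrality | Power |
|---|---|---|---|
| none (unadjusted) | 17.00 | 2.185 | 69.5% |
| 0.1 | 16.91 | 2.196 | 69.9% |
| 0.3 | 16.22 | 2.290 | 73.0% |
| 0.5 | 14.72 | 2.522 | 80.0% |
| 0.7 | 12.14 | 3.059 | 91.5% |

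Simulation, which also carries the small loss from chance imbalance in T1, gives 72%, 80% and 91% at r = 0.3, 0.5 and 0.7.

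**3. If the t-test is on change.** SD of change = 17 × √(2(1 − r)), giving 20.11, 17.00 and 13.17 at r = 0.3, 0.5 and 0.7. Power is 57%, 69.5% and 87%, below ANCOVA at each value. If 17 is instead the SD of change, the change-score test has the 69.5% and ANCOVA has 85%, 80% and 76% at the same correlations. ANCOVA is ahead under either reading; the size of the gain differs.

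**4. Adjust only if the T1 test is significant (T1 score the only candidate; 20,000 simulated trials per setting).**

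| r | Unadjusted power | Always adjust | Triggered rule | Type I error of triggered rule |
|---|---|---|---|---|
| 0.3 | 69% | 72% | 70% | 4.9% |
| 0.5 | 70% | 80% | 70% | 4.5% |
| 0.7 | 70% | 91% | 71% | 4.1% |

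With eight independent baseline variables, one of them prognostic at r = 0.5, the triggered rule has 69% power against about 80% for always adjusting. Its type I error at the margin is about 4.5%. The noninferiority conclusion differs from the unadjusted one in about 5% of trials when the true difference is 0.

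**5. What the baseline tests detect.** The chance that at least one of k independent null tests is significant is 1 − 0.95^k: 23% for k = 5, 34% for k = 8, 40% for k = 10. A 0.5 SD difference between arms, with 26 per arm and a two-sided 5% test, is flagged 42% of the time.

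**The case against.** The strongest case against has four parts.

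- **The T1 score may be used after all.** A reader might infer that the plan discards it. The article does not support that. The missing-data rule and the cost analysis are both worded in terms of change in score, so a t-test on change is as plausible as one on T2, and a change score uses T1. This stands. What remains is that the choice is unstated and that neither t-test is as efficient as ANCOVA.
- **A p < 0.05 trigger for entering covariates is not written down.** A reader might infer it from the baseline t-tests and chi-squared tests. That is a fair reading, but the article gives no threshold and no method, and the sentence could even refer to secondary analyses. This also stands, and the vagueness is part of the problem.
- **A condensed article leaves the model to the full protocol or SAP.** A t-test sample-size calculation does not bind the final analysis, and the absence of an ANCOVA specification alone would be no finding. But the article does more than stay silent: it commits to a correction that depends on observed imbalance.
- **The harm may be small.** The unadjusted test is valid under randomisation. A reader might infer that the trigger inflates false noninferiority claims; the simulations show the opposite for a mechanically applied rule (4.1% to 4.9%). The efficiency gain rests on an unknown correlation. T1 is taken 1 to 2 weeks after fracture, in patients fitted with a splint, so the T1 Constant score may be compressed and weakly related to T2. At r = 0.1 the gain is under half a percentage point. All of this stands.

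**Conclusion.** The point holds in a limited form. The article states a data-dependent adjustment rule without characteristics, threshold or method, does not say whether T2 or change is compared, and gives the T1 Constant score no prespecified role as a covariate. The primary noninferiority estimate is therefore not fixed before the data are seen.

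The demonstrable cost is efficiency, and its size is illustrative only: from almost nothing at a correlation of 0.1 to roughly 10 percentage points of power at 0.5 and more than 20 at 0.7, if SD 17 is the T2 SD. The cost of discretion in choosing an unnamed remedy is real but cannot be quantified from the article. The defect does not invalidate the trial, but it should be corrected because the correction is nearly free.

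**What to change.** 1. Name one primary model in advance: an ANCOVA of T2 Constant score on arm, with T1 Constant score as covariate, used whatever the observed balance.
2. Test noninferiority on the adjusted difference, with the 10.3-point margin and one-sided alpha of 0.05 applied to its confidence limit.
3. Report baseline characteristics descriptively, without tests between arms, and delete the sentence on corrections after an observed imbalance.
4. DASH and range of motion can be handled in the same way with their own T1 values.

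The cost is a change of wording and one degree of freedom (49 instead of 50 in the primary model). No extra participants or measurements are needed, since the T1 values are already collected. The change should be made and dated before outcome data are compared by arm.

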### Trial status

Recruitment has begun since June 2015.

## Abbreviations

CIUSSS de l’Estrie CHUS: Centre intégré universitaire de santé et de services sociaux de l’Estrie - Centre hospitalier universitaire de Sherbrooke
CLINIC: Conventional face-to-face rehabilitation in a clinic
CURE: Clinique universitaire de réadaptation de l’Estrie
DASH: Disability of the Arm, Shoulder and Hand questionnaire
RCT: Randomised clinical trial
T1: Baseline evaluation (pre-intervention)
T2: Post-intervention evaluation
TELE: In-home telerehabilitation
